#### Procedures for LDF examination and moxibustion

2.6.1

A four-channel LDF (PeriFlux System 5000, Sweden) will be used to measure the microcirculatory characteristics of the Heart and Lung meridians, which could monitor 4 measurement sites simultaneously. The participants will be asked to stabilize for 15 minutes in a supine position in the experimental room before LDF examination. They will be informed to keep silent and normal breath and avoid limb movement during the whole measurement period. The probes will be placed at corresponding measurement sites. Blood flow curve and microcirculatory flux, expressed as blood perfusion units (PU), will be assessed.

(1)Healthy control group and CSAP groupThe probes will be left at 4 measurement sites (Fig. 2), which include “Shenmen” (HT7) and “Shaohai” (HT3) of the Heart meridian, “Taiyuan” (LU9) and “Chize” (LU5) of the Lung meridian. The blood flow curve and PU will be recorded for 5 minutes.(2)Healthy intervention groupTwo sessions of moxibustion will be performed in the Heart meridian and Lung meridian, respectively. The washout period between the two sessions is at least one day to avoid inter-experiment interference. The intervention procedures and LDF measurement sites are shown in Figure 3.

**Figure 2 F2:**
[figure not shown]
The LDF measurement sites of the healthy control group and CSAP group. CSAP = chronic stable angina pectoris, LDF = laser doppler flowmetry.

**Figure 3 F3:**
[figure not shown]
The intervention procedure of the healthy intervention group. (A) Moxibustion site of the Heart meridian and LDF measurement sites of the Heart and Lung meridians; (B) Moxibustion site of the Lung meridian and LDF measurement sites of the Heart and Lung meridians. CSAP = chronic stable angina pectoris, LDF = laser doppler flowmetry.

(1)Intervention in the Heart meridian: By igniting the moxa stick and inserting it into a homemade moxibustion holder to adjust appropriate angle and height, moxibustion will be performed at “Shaohai” (HT3) of the Heart meridian for 15 minutes. During moxibustion, LDF probes will be placed in three measurement sites, which include the midpoint of the Heart meridian along the left forearm (ie, midpoint of between HT3 and HT7), “Chize (LU5)” of the Lung meridian, and the midpoint of the Lung meridian along the left forearm(ie, midpoint of between LU5 and LU9). The intervention procedure and LDF measurement sites are shown in Figure 3 (A). The measurement time points include 5 minutes before moxibustion, 15 minutes during moxibustion and 5 minutes after removal of moxibustion.(2)2)Intervention in the Lung meridian: The moxibustion acupoint is “Chize” (LU5) of the Lung meridian. The LDF examination, moxibusition procedure and measurement time points are the same as 1). During moxibustion, the LDF probes will detect the blood perfusion in three measurement sites, which include the midpoint of the Lung meridian along the left forearm(i.e. midpoint between LU5 and LU9), “Shaohai” (HT3) of the Heart meridian, and the midpoint of the Heart meridian along the left forearm (i.e. midpoint between HT3 and HT7. The intervention procedure and LDF measurement sites are shown in Figure 3(B).

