### Data collection and statistical analysis

2.10

Statistical analysis will be performed using the statistical software package SPSS 17.0 for Windows (SPSS Inc., Chicago, IL) by third party statisticians who does not participant in this trial. Numeric data with normal distribution will be expressed as mean ± standard deviations, whereas data with skewed distribution as median with 95% confidence intervals. Categorical data will be shown as counts and percentages.

Repeated measures ANOVA will be used to assess change in continuous variables before and after intervention. The paired samples *t*-test will be used to compare the changes within the groups, whereas the independent samples t-test will be employed for comparisons between the groups. Within-group/between-group comparison regarding data with skewed distribution is assessed using non-parametric test. Between-group differences for baseline dichotomous variables, such as gender and ages, will be tested using the Chi-square test. A *P* value of less than .05 will be considered statistically significant.

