Second, our study design presents different comparisons to verify the specificity for the meridian-visceral association and site-to-site association between 2 specific meridians, which is a highlight. The theory of meridian-viscera association emphasizes the diagnostic and therapeutic values based on the mutual relation in physiology and the interaction effect in pathology between meridians and viscera. In details, visceral physiological functions and pathological changes will manifest in the corresponding meridians or the acupoints^[33]^ and the visceral disorders can be treated with the involved meridian and acupoints.^[34]^ A number of modern studies have confirmed the relatively specific relationship between meridians and viscera, and the modulating effect of acupoints/meridians for the visceral function^[35–37]^ On 1 hand, we hypothesize that the change in microcirculatory characteristics of the Heart meridian between the healthy control group and CSAP group is more significant than that of the Lung meridian. Thus, the specificity for the meridian-visceral association will be investigated by comparing the microcirculatory difference between the Heart and Lung meridians in the healthy control group and CSAP group. We present such a comparison (healthy control group vs CSAP group) to verify the sensitization phenomena of meridians under pathological circumstances as well as the specificity of meridian-visceral association.

On the other hand, we hypothesize that the change in microcirculatory characteristics in relevant sites of the stimulated meridian is more significant than that of the non-stimulated meridian in the healthy control group. Thus, the specificity for the site-to-site association will be explored by comparing the microcirculatory change between the Heart and Lung meridians by performing moxibustion in the Heart meridian and Lung meridian, respectively. It should be noted that moxibustion intervention is applied only in the healthy control group rather than the CSAP group. By such a study design and comparison, we attempt to confirm whether meridians are not only sensitized in pathological conditions but also activated in physiological state, which is an important issue to be solved in meridian researches.

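### In each moxibustion session the unheated meridian has an extra, unmatched probe site, and the plan does not fix which sites the site-to-site comparison uses

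*Protocol article*

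**What the plan says.** Section 2.6.1, including the text under Figure 3, describes two sessions per participant in the healthy intervention group, at least one day apart. Each is recorded for 5 minutes before, 15 minutes during and 5 minutes after moxibustion.

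- Heart session: heat is applied at "HT3) of the Heart meridian for 15 minutes". One probe is on the heated meridian: "During moxibustion, LDF probes will be placed in three measurement sites, which include the midpoint of the Heart meridian along the left forearm". The other two are at LU5 and at the Lung midpoint: "of the Lung meridian, and the midpoint of the Lung meridian along the left forearm(ie, midpoint of between LU5 and LU9".
- Lung session: heat is applied at "LU5) of the Lung meridian. The LDF examination, moxibusition procedure and measurement time points are the same as 1". One probe is on the heated meridian, at "the midpoint of the Lung meridian along the left forearm(i.e. midpoint between LU5 and LU9". The other two are at HT3 and at the Heart midpoint.

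The flowmeter is one "which could monitor 4 measurement sites simultaneously", so one channel is idle in each session.

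The Discussion hypothesises that the "change in microcirculatory characteristics in relevant sites of the stimulated meridian is more significant than that of the non-stimulated meridian". It places this in the healthy control group, whereas section 2.6.1 gives the sessions to the healthy intervention group. That is a separate inconsistency, and I follow section 2.6.1 here. Section 2.7 makes perfusion at the relevant sites primary without listing them. Section 2.10 says "Repeated measures ANOVA will be used to assess change in continuous variables before and after intervention", with paired t-tests for changes within groups and independent t-tests between groups. It names neither site nor session as a factor.

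**The concern.** Site-to-site specificity is one of the two stated aims, and it rests on comparing a heated with an unheated meridian. In each session these are not sampled alike: one mid-forearm site on one side, a mid-forearm site plus an end site on the other. If the end site responds differently from a midpoint for reasons unrelated to meridians, such as local spread of heat, a comparison that includes it carries that difference into the result. A stronger response at the end site would hide a true meridian effect; a weaker one would mimic it.

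The written analysis does not settle the matter. A before/after test at each site shows whether that site changed. One site changing more significantly than another in separate tests is not a test of the difference between them. Section 2.5 adds that the statisticians will be blinded to the study protocol, so they cannot be expected to work out from the probe layout which sites are matched. With several pairings open, the choice could be made after the data are seen.

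**Working it through.** **Step 1: count the sites (section 2.6.1).**

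| Session | Heat | Heated-meridian sites | Unheated-meridian sites |
|---|---|---|---|
| Heart | HT3 | Heart midpoint | Lung midpoint, LU5 |
| Lung | LU5 | Lung midpoint | Heart midpoint, HT3 |

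The count is 1 against 2 in both sessions. HT3 and LU5 have no heated counterpart in this group. Both midpoints appear in both sessions, each with a 5-minute baseline.

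**Step 2: bias with no meridian effect.** Let E be the response at the end site minus that at a midpoint.

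- Heated midpoint minus unheated midpoint: 0 (position matched)
- Heated midpoint minus mean of the two unheated sites: 0 − (0 + E)/2 = −E/2
- Heated midpoint minus unheated end site: −E

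**Step 3: how often the null is rejected.** The 40 per group comes from section 2.2 and the 0.05 level from section 2.10. The protocol gives no effect size, SD or power, so there is no power calculation to reproduce. Assumptions: two-sided test, SD of change 1 at each site, within-person correlation ρ of 0.3 to 0.7. The SD of the pooled difference is then √[1 + (1 + ρ)/2 − 2ρ] = √[1.5(1 − ρ)]. Paired t-tests, 20,000 simulated trials per setting, no meridian effect:

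| E (SD) | Midpoint vs midpoint | Midpoint vs mean of two: ρ = 0.3 | ρ = 0.5 | ρ = 0.7 |
|---|---|---|---|---|
| 0 | about 5% | 5.1% | 5.2% | 5.1% |
| 0.25 | about 5% | 11.3% | 14.4% | 21.3% |
| 0.5 | about 5% | 32.3% | 42.6% | 63.0% |
| 1.0 | about 5% | 85.6% | 94.5% | 99.6% |

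For positive E these rejections run against the trial's hypothesis (masking); for negative E they run in its favour.

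**Step 4: what the midpoint contrast leaves behind.** Take the double difference D = (Heart − Lung midpoint, Heart session) − (Heart − Lung midpoint, Lung session). A fixed difference between the two sites appears in both brackets and cancels. Distance from the heat does not cancel.

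Illustrative geometry, not from the protocol: two parallel 24 cm forearm lines whose upper ends lie 4 to 8 cm apart. The own-meridian midpoint is 12 cm from the heat. The other midpoint is √(12² + 4²) = 12.6 cm to √(12² + 8²) = 14.4 cm away. Suppose response depends only on distance and decays exponentially, with +40% at the end site and +10% at 12 cm (also assumed):

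- 4 cm gap: rate ln 4/(12 − 4) = 0.173 per cm; other midpoint 10 × exp(−0.173 × 0.65) = 8.9%; D = 2 × (10 − 8.9) ≈ +2 points
- 8 cm gap: rate ln 4/(12 − 8) = 0.347 per cm; other midpoint 10 × exp(−0.347 × 2.42) = 4.3%; D = 2 × (10 − 4.3) ≈ +11 points

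The own-meridian midpoint is nearer the heat in both sessions, so the two advantages add. The residual favours the hypothesis.

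**Step 5: precision.** With 40 participants, a one-sample test of D detects about 0.45 SD of D (two-sided 0.05, 80% power).

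**The case against.** The strongest reply is that no confounded comparison is planned. Nothing in the article averages the end site with a midpoint, the matched midpoints are recorded in both sessions, and the paired t-test or a repeated measures ANOVA with added factors could carry the right contrast. Contrast coding is commonly left to an analysis plan, the article condenses a fuller protocol, and the Discussion calls the study a pilot. Not probing the heated point may also be deliberate or unavoidable.

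Most of this stands. A reader might infer that the design confounds heated versus unheated with probe position, so that the second aim cannot be answered. The documents do not support that: confounding enters only if HT3 or LU5 is pooled or used as the comparator, which the text neither requires nor excludes. Nor does the visible text say that HT3 and LU5 lie at the same level. It only makes them end points of the lines whose midpoints are probed, and Table 2 and Figure 3 are not shown.

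Two things survive. Probe placement is a design feature that the article does fix, and it creates an imbalance that the stated hypothesis and tests ignore. And leaving the contrast to be worked out later sits badly with statisticians who are blinded to the protocol.

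**Conclusion.** The point holds in a limited form. Each session has one heated-meridian site against two unheated-meridian sites, and the additional site has no heated counterpart. The text does not fix a comparison that avoids it. Using that site biases the contrast by −E/2 when the two unheated sites are averaged and by −E when it is used alone. At E = 0.5 SD, averaging raises rejection of a true null from about 5% to 32–63%. The site and session counts come from the protocol; E, the SDs, the correlations, the centimetre distances and the percentage responses are assumptions.

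It would be equally wrong to infer that the midpoint contrast is free of bias. It removes the unmatched site and fixed site differences, but the own-meridian midpoint is probably nearer the heat in both sessions. In the illustration this leaves about +2 to +11 points in favour of the hypothesis with no meridian effect. A positive result on the midpoints alone would therefore not separate a meridian effect from spread of heat by distance.

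**What to change.** 1. Name the primary site-to-site contrast. For each participant, take change in log PU from the 5-minute baseline and compute (Heart midpoint − Lung midpoint in the Heart session) − (the same in the Lung session). Test it with a one-sample t-test, or as the session-by-site term of a mixed model with session and period. If every participant has the sessions in the same order, period cannot be separated from session; a period shift common to both midpoints still cancels in the contrast.
2. Report HT3 and LU5 separately, outside the primary test.
3. State that the contrast removes fixed site differences but not distance from the heat. Either use the idle fourth channel for an off-meridian forearm site at the same distance from the heat as the own-meridian midpoint, or limit the conclusion accordingly. The off-meridian site matches distance but not fixed site differences, so the two contrasts should be read together.
4. Give the contrast in writing to the third-party statisticians before analysis.

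Cost: items 1, 2 and 4 need wording only and use data already planned. The end-site data leave the primary test. The fourth probe needs minor extra set-up on existing equipment and applies only to sessions not yet run, as the article describes the trial as ongoing.

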#### Locations of the acupoints and LDF measurement sites

2.6.2

The locations of the acupoints and LDF measurement sites of the Heart and Lung meridians are displayed in Table 2.

**Table 2 T2:**
[figure not shown]
Location of acupoints and LDF measurement sites of the heart and lung meridians.

#### Concomitant treatments

2.6.3

During the study period, all the participants in the CSAP group will maintain their previous treatment regimen. If additional medications or other treatments are used during the study period due to any reasons, the details (eg, the name, administration time and dosage of the medication) should be documented.

Besides, participants in the healthy control group and healthy intervention group should not take any medications during the full study period. If drugs or other treatments are adopted due to sudden diseases, researchers will evaluate whether they should be withdrawn from the study.

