##### Inclusion criteria for healthy adults

2.3.1.1

(1)Healthy adults should provide a recent medical examination report to confirm they have not any cardiovascular, respiratory, digestive, urinary, hematological, endocrine, and neurological disease;(2)Age ≥20 years, male or female;(3)Participants have clear consciousness and could communicate with others normally;(4)Participants could understand the full study protocol and written informed consent is signed.

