##### Exclusion criteria for the CSAP patients

2.3.2.2

(1)Patients have acute coronary syndrome and severe arrhythmias;(2)Patients’ chest pain is caused by valvular heart disease, hypertrophic cardiomyopathy and dilated cardiomyopathy;(3)Patients’ chest pain is caused by non-cardiac disease;(4)Patients have concomitant lung diseases, such as obstructive pulmonary disease;(5)Patients have serious concomitant conditions and fail to treat them effectively, such as diseases of the digestive, urinary, respiratory, haematological, and nervous system;(6)Patients have mental illness, severe depression, alcohol dependence or history of drug abuse;(7)Pregnant or lactating patients;(8)Patients are participating in other trials.

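### Treated CSAP patients are compared with unmedicated healthy adults, so a single-site perfusion difference cannot be attributed to heart disease alone, and the within-person contrast that would partly protect the comparison is not named

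*Protocol article*

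**What the plan says.** **Treatment (section 2.6.3).** In the patient group, "all the participants in the CSAP group will maintain their previous treatment regimen". For the healthy groups, "participants in the healthy control group and healthy intervention group should not take any medications during the full study period". A healthy participant who needs a drug for a sudden illness is assessed for withdrawal and may be kept.

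**Comorbidity (sections 2.3.1.1 and 2.3.2.2).** Healthy adults need a medical report showing that "they have not any cardiovascular, respiratory, digestive, urinary, hematological, endocrine, and neurological disease". The corresponding CSAP exclusion is narrower: "Patients have serious concomitant conditions and fail to treat them effectively, such as diseases of the digestive, urinary, respiratory, haematological, and nervous system". Endocrine disease is not among its examples.

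**Outcome and analysis (sections 2.7 and 2.10).** The primary outcomes are the blood flow curve and PU at sites on the two meridians. Groups are compared by independent samples t-test, and changes within groups by paired t-test. Repeated measures ANOVA is named for change before and after intervention. No covariate and no group-by-meridian test is named.

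**Claim (Discussion).** The hypothesis is that the control-versus-CSAP difference is greater on the Heart than on the Lung meridian. The comparison is meant "to verify the sensitization phenomena of meridians under pathological circumstances as well as the specificity of meridian-visceral association".

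**The concern.** The groups are formed by disease status, not by randomisation, and two other things change with disease: background treatment and permitted comorbidity. The outcome is skin blood flow, which vasoactive drugs and diabetes can plausibly alter directly. That premise is general physiology, not something the protocol states. The protocol does accept that outside exposures disturb the measurement, because section 2.6 restricts coffee, tea, alcohol, smoking, food and exercise before the recording.

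If drugs or treated comorbidity shift PU, a group difference at a Heart meridian site would appear with no effect of the heart disease itself. Read as the Discussion proposes, it would be reported as meridian sensitization. Covariate adjustment cannot repair this for treatment, because hardly any control will be on medication and the data cannot separate drug from disease.

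**Working it through.** **Step 1. What differs by group.**

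| | Healthy control | CSAP |
|---|---|---|
| Background treatment | Should take none (2.6.3) | Usual regimen continues (2.6.3) |
| Serious, ineffectively treated endocrine disease | Excluded (2.3.1.1) | Could be excluded, since the list is open (2.3.2.2) |
| Effectively treated or non-serious endocrine disease | Excluded (2.3.1.1) | Eligible (2.3.2.2) |

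Treatment therefore follows group almost completely, and the third row is one-sided. Age limits differ too: healthy adults are admitted at "Age ≥20 years, male or female" with no upper limit, and CSAP patients at 35 to 75. The article describes no matching.

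**Step 2. Sample size.** The plan's figure is 3 × 40 = 120 (section 2.2). It rests on similar studies, with no effect size or SD, so there is no power calculation to reproduce. The figure used below is 40 per group.

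**Step 3. Single-site comparison.** Assume no disease effect and a shift of δ SD in PU caused by drugs or comorbidity alone. δ is an assumption; the documents give none. Sidedness is not stated, so a two-sided 5% test is assumed. The standard error of the difference is √(2/40) = 0.2236 SD, so

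rejection rate ≈ Φ(δ/0.2236 − 1.96) + Φ(−δ/0.2236 − 1.96).

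| δ (SD) | δ/0.2236 | Normal approximation | t-test, 78 df |
|---|---|---|---|
| 0 | 0 | 5% | 5% |
| 0.2 | 0.894 | 15% | 14% |
| 0.3 | 1.342 | 27% | 26% |
| 0.4 | 1.789 | 43% | 42% |
| 0.5 | 2.236 | 61% | 60% |

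Here δ is the average shift over the whole CSAP group. If only half the patients carried a factor worth 0.5 SD, then δ = 0.5 × 0.5 = 0.25 and the rate is about 20% by the normal approximation.

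**Step 4. Heart-minus-Lung contrast.** Let H and L be one person's PU on the two meridians. If drugs or comorbidity multiply both by the same factor k, then log(kH) − log(kL) = log H − log L. The shift cancels and the test keeps its 5%.

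If the shift differs between meridians by 0.3 SD of log PU, the SD of the within-person difference is √(2(1 − ρ)), where ρ is the assumed within-person correlation:

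| ρ | SD of difference | Standardised shift | Rejection (normal approximation) |
|---|---|---|---|
| 0.3 | 1.183 | 0.3/1.183 = 0.254 | 21% |
| 0.5 | 1.000 | 0.300 | 27% |
| 0.7 | 0.775 | 0.3/0.775 = 0.387 | 41% |

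The contrast removes shifts common to all sites but not site-specific ones.

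**Step 5. Is the contrast in the plan?** The hypothesis in the Discussion implies it. The tests in section 2.10 do not name it. Comparing groups site by site, or meridians within each group, and then setting the p-values side by side does not test whether the group difference is larger on one meridian.

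**The case against.** The strongest reply is that the stated hypothesis already uses the Lung meridian as an internal control, so the 26% to 60% figures do not describe it. This stands. Those rates apply only to single-site group comparisons, and a reader who inferred that the specificity hypothesis is equally exposed would go too far. The protection is partial, however, because section 2.10 does not name the contrast and nothing shows that drug effects are equal across sites. It gives no protection to the sensitization reading, which rests on the group difference itself.

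Other stronger readings are tempting and not supported:

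- **No control is medicated.** The rule permits keeping a control who takes a drug for a sudden illness, so exposure is not strictly zero. Nor do the documents give the proportion of CSAP patients on treatment.
- **Endocrine disease is excluded only in controls.** The CSAP list is introduced by examples, so serious, ineffectively treated endocrine disease could be excluded there too.
- **Background drugs go unrecorded.** The article states a documentation rule for additional treatments only. It is a condensed text, its schedule table is not shown, and case report forms are mentioned. Silence here does not show a gap.
- **Subgroups by drug class would settle the matter.** Splitting 40 patients leaves small groups, and drug class may track severity.

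The Discussion does call the study a pilot and asks for caution because of unnamed factors. That caveat is too general to cover this point.

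**Conclusion.** The point holds in a limited form. A control-versus-CSAP difference in PU at any site mixes disease, background treatment and one-sided treated comorbidity, so the sensitization claim is not supported by the independent t-test. Under an assumed shift of 0.3 to 0.5 SD, about 26% to 60% of single-site tests would be significant with no disease effect; at 0.2 SD the figure is about 14%. These sizes illustrate the risk and do not estimate it.

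The specificity hypothesis is better placed. A shift proportional at all sites leaves its error rate at 5%, provided the log contrast is the analysis. A shift that differs between meridians by an assumed 0.3 SD gives about 21% to 41%.

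Keeping patients on their treatment is not the fault. The fault is a causal reading that this comparison cannot carry. This should be corrected, but it does not stop the study.

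**What to change.** 1. **Primary control-versus-CSAP analysis.** For each person, take the mean log PU of HT7 and HT3 minus the mean log PU of LU9 and LU5, and compare this difference between groups. This is the group-by-meridian interaction and tests the Discussion's hypothesis directly. State that it removes shifts proportional at all sites but not site-specific ones.
2. **Single-site group differences.** Report them as descriptive.
3. **Conclusion.** Word it as an association in treated CSAP patients versus unmedicated healthy adults. Name background treatment and treated comorbidity as specific limitations, and drop the language of verification.
4. **Optional sensitivity check.** Repeat the contrast without CSAP patients who have diabetes. This addresses one comorbidity and does not separate drug from disease.

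Treatment, eligibility and sample size stay as they are. The cost is one extra analysis and a narrower claim.
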